### Primary endpoint

The primary endpoint of this study is the 4.5-year disease-free survival (DFS) rate, which is defined as the probability of no evidence of disease recurrence from the date of operation to the postoperative date of 4.5 years.

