### Secondary endpoints

The secondary endpoints include the 4.5-year overall survival (OS) rate, recurrence pattern, and safety. The OS rate of 4.5 years is defined as the probability of survival from the date of operation to the postoperative date of 4.5 years. The recurrence pattern is evaluated by the location of recurrence in patients with confirmation of recurrence. Safety will be assessed by the rate of intraoperative organ injury, early (within 4 weeks after surgery), and late (from 4 weeks to 6 months after surgery) complications graded by Memorial Sloan Kettering Cancer Center (MSKCC) grading criteria [15]. Also, a detailed pathologic report, estimated blood loss, operation time, transfusion, and hospitalisation days would also be evaluated.

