### Sample size

Based on our previous study, the 4.5-year DFS rate of patients with stage IB1 disease who underwent the abdominal radical hysterectomy was 90.9% [16], and the non-inferiority margin was 7.2% for MIS in the LACC trial [3]. Based on these results, we hypothesised that the 4.5-year DFS rate of patients who would undergo MIS using an endoscopic stapler would be the same value of 90.9%, and if the DFS does not differ by more than 7.2%, abdominal radical hysterectomy and MIS using an endoscopic stapler would be equivalent to each other. Therefore, the null hypothesis (H0) for this study is that the 4.5-year DFS rate of patients who would undergo MIS using an endoscopic stapler is 83.7%, whereas the alternative hypothesis (H1) is that the 4.5-year DFS rate of the patients is 90.9%. When we consider a three-year accrual and 4.5-year follow-up, at least a total of 13 events must happen, requiring a total of 111 patients assuming a statistical power of 80% and the one-tailed test of 5% significance. A total of 124 patients is needed, considering a drop-out rate of 10%.

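### The primary endpoint is called disease-free survival but counts recurrence only, so its comparison with external DFS figures favours success if those figures count deaths

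*Protocol article*

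**What the plan says.** Under Primary endpoint, the 4.5-year DFS rate is "defined as the probability of no evidence of disease recurrence from the date of operation to the postoperative date of 4.5 years". Recurrence is the only event named. Under Secondary endpoints, death enters through overall survival alone: "The OS rate of 4.5 years is defined as the probability of survival from the date of operation to the postoperative date of 4.5 years". No other section adds death to the DFS definition.

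Under Sample size, the endpoint is set against two outside figures. The first comes from the group's previous study: "the 4.5-year DFS rate of patients with stage IB1 disease who underwent the abdominal radical hysterectomy was 90.9" per cent. The second is taken from an earlier randomised trial: "the non-inferiority margin was 7.2% for MIS in the LACC trial". Their difference gives the null hypothesis, that "the 4.5-year DFS rate of patients who would undergo MIS using an endoscopic stapler is 83.7" per cent; under the alternative the rate is 90.9%. The article does not define DFS for either source.

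Statistical methods names Kaplan-Meier estimation for DFS and OS and does not say how a death without recurrence is treated. The Discussion defends the 4.5-year time point partly by comparability with the LACC trial.

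**The concern.** The label and the definition describe different quantities. A DFS rate that counts recurrence or death cannot exceed the overall survival rate at the same time. The quantity defined here can, because a perioperative death, a treatment-related death or a death before recurrence is documented is not a failure. If such deaths are censored, the Kaplan-Meier curve estimates freedom from recurrence in a hypothetical population in which nobody dies first.

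In a randomised comparison both arms would share the definition. Here the comparator is a fixed number from elsewhere, so the test is fair only if that number was built from the same events, and nothing in the article secures this. Any error can go only one way: leaving deaths out raises the observed rate or leaves it unchanged. With a margin of 7.2 points and about 13 planned events, one to three uncounted deaths would matter.

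**Working it through.** **Inputs from Sample size.** H0 83.7%, H1 90.9%, one-sided 5%, power 80%, accrual 3 years, follow-up 4.5 years, 13 events, 111 patients, 124 with 10% drop-out. The article does not name the test or the survival distribution. I assume exponential survival, uniform accrual and a minimum follow-up of 4.5 years.

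**Step 1: reproduce the plan's figures.**
- Yearly hazards: −ln(0.837)/4.5 = 0.03954 under H0 and −ln(0.909)/4.5 = 0.02120 under H1. Ratio 0.02120/0.03954 = 0.536.
- Event probability under H1: v1 = 1 − (e^(−4.5λ) − e^(−7.5λ))/(3λ) with λ = 0.02120, which is 0.1193. The same formula with the H0 hazard gives 0.2107.
- Mean H0 cumulative hazard in an H1 population: v0 = 0.1193/0.536 = 0.2225.
- Variance under H1 of (event indicator − H0 cumulative hazard): s1 = 0.1332, by simulation.
- One-sample log-rank: n = (1.645·√v0 + 0.842·√s1)² / (v0 − v1)² = 110.2, so 111 patients. Expected events: 110.2 × 0.1193 = 13.1.
- Drop-out: 111/0.9 = 123.3, so 124.

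All three planned figures reproduce; there is no arithmetic error. A one-sample test of a proportion would need about 139 patients, so the log-rank form is the one that fits.

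**Step 2: effect of leaving deaths out if the benchmark counts them.** Let true DFS, counting deaths, be exactly 83.7%, the boundary at which success should be declared at most 5% of the time. Let q be the part of the 16.3-point loss made up of deaths without recurrence. The documents give no value for q, so a range of 0.5 to 3 points is assumed. The counted hazard is the H0 hazard times (1 − q/0.163). With such deaths censored, the Kaplan-Meier rate tends to 0.837^(1 − q/0.163). For example, at q = 0.02 the exponent is 1 − 0.1227 = 0.8773, and 0.837^0.8773 = 0.855.

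The type I error is the chance that (O − E)/√E < −1.645 with 111 patients, where O is the observed number of recurrences and E the number expected under H0, by simulation.

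| q (points) | Patients of 111 | Recurrence-only rate | Type I error |
|---|---|---|---|
| 0 | 0 | 83.7% | 4.3% |
| 0.5 | 0.6 | 84.2% | 5.8% |
| 1 | 1.1 | 84.6% | 7.6% |
| 2 | 2.2 | 85.5% | 12.8% |
| 3 | 3.3 | 86.5% | about 20% |

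A normal approximation to the same test gives 5.0%, 6.4%, 8.2%, 13.1% and 20.2%. At q = 3 points the overstatement is 86.5 − 83.7 = 2.8 points, and 2.8/7.2 is 39% of the margin.

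**Step 3: effect if the benchmark counts recurrence only.** Trial and benchmark then use the same events and the mismatch is zero for every q.

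**The case against.** The strongest reply is that no mismatch has been shown. A reader might infer that the result will be biased upward. The article does not support that: it gives no event definition behind the 90.9% or the 7.2 points. The 90.9% comes from the group's own earlier study, which may have used the same recurrence-only rule. The Background also describes a trial of disease-free survival and reports its result as a higher risk of recurrence, which suggests loose use of the terms. This stands, and it makes the bias conditional.

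A reader might also infer that deaths are to be censored. The article does not say so; detailed censoring rules are commonly left to the full protocol or analysis plan. This stands too, but it does not rescue the definition. Whether such deaths are censored or carried forward as disease-free, they are not events under the stated rule, and a later document that counted them would change the published primary endpoint.

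Nor should the decision be read as turning on 11 versus 12 failures among 111 patients, the cut-off of an exact binomial test. The article names no such rule, and it would have only 69% power at 90.9%, not the planned 80%.

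Finally, the range for q is assumed. Exclusion of patients with serious systemic disorders incompatible with the study argues against its upper end, and at 0.5 points the effect is small.

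**Conclusion.** The point holds in conditional form. What is established from the text is that the primary endpoint carries a DFS label, that its only definition names recurrence alone, and that it is tested in a single arm against DFS figures whose events are not given. What is not established is that the comparison is biased; that depends on whether the 90.9% and the 7.2 points count deaths.

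If they do, the bias is towards success. Under exponential survival, uniform accrual, the one-sample log-rank test and an assumed 0.5 to 3 points of death without recurrence, the one-sided type I error rises from about 4% to between about 6% and 20%. If they do not, the bias is zero. The event set should be settled before the primary analysis.

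**What to change.** Define DFS as time from operation to first recurrence or death from any cause, estimated at 4.5 years. Confirm that the 90.9% and the 7.2-point margin rest on the same events. If the 90.9% does not, recompute it from the sponsor's earlier cohort under the new definition and restate H0, H1 and the sample-size figures. Report recurrence separately as a cumulative incidence with death as a competing event.

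The cost is small: a sentence in the endpoint definition, a check of two sources and possibly a re-analysis of an existing cohort. Deaths are already needed for overall survival. If both outside figures already count deaths, the 13 events, 111 patients and 124 in total stand unchanged. The downside is that the DFS estimate may be slightly lower.

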### Secondary endpoints

The secondary endpoints include the 4.5-year overall survival (OS) rate, recurrence pattern, and safety. The OS rate of 4.5 years is defined as the probability of survival from the date of operation to the postoperative date of 4.5 years. The recurrence pattern is evaluated by the location of recurrence in patients with confirmation of recurrence. Safety will be assessed by the rate of intraoperative organ injury, early (within 4 weeks after surgery), and late (from 4 weeks to 6 months after surgery) complications graded by Memorial Sloan Kettering Cancer Center (MSKCC) grading criteria [15]. Also, a detailed pathologic report, estimated blood loss, operation time, transfusion, and hospitalisation days would also be evaluated.

### Sample size

Based on our previous study, the 4.5-year DFS rate of patients with stage IB1 disease who underwent the abdominal radical hysterectomy was 90.9% [16], and the non-inferiority margin was 7.2% for MIS in the LACC trial [3]. Based on these results, we hypothesised that the 4.5-year DFS rate of patients who would undergo MIS using an endoscopic stapler would be the same value of 90.9%, and if the DFS does not differ by more than 7.2%, abdominal radical hysterectomy and MIS using an endoscopic stapler would be equivalent to each other. Therefore, the null hypothesis (H0) for this study is that the 4.5-year DFS rate of patients who would undergo MIS using an endoscopic stapler is 83.7%, whereas the alternative hypothesis (H1) is that the 4.5-year DFS rate of the patients is 90.9%. When we consider a three-year accrual and 4.5-year follow-up, at least a total of 13 events must happen, requiring a total of 111 patients assuming a statistical power of 80% and the one-tailed test of 5% significance. A total of 124 patients is needed, considering a drop-out rate of 10%.

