**Methods:**

This trial is a prospective, multi-centre, open-label, single-arm, non-inferiority phase II study. The nine organisations will participate in this trial after the approval of the institutional review board. Major eligibility criteria include women aged 20 years or older with cervical cancer stage IB1 squamous cell carcinoma, adenocarcinoma, or adenosquamous carcinoma according to the revised 2009 FIGO staging system who will undergo type B2 or C hysterectomy by MIS. The primary endpoint is the 4.5-year disease-free survival (DFS) rate between abdominal radical hysterectomy and MIS using an endoscopic stapler. For calculating the sample size, we hypothesised that the 4.5-year DFS rate after MIS using an endoscopic stapler is assumed to be the same after abdominal radical hysterectomy at 90.9%, and the non-inferiority margin was 7.2%. When we consider a three-year accrual and 4.5-year follow-up, at least 13 events must happen, requiring a total of 111 patients assuming a statistical power of 80% and the one-tailed test of 5% significance. A total of 124 patients is needed, considering a drop-out rate of 10%.

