### Statistical methods

The efficacy analysis will be performed in both per-protocol and intention-to-treat populations. Kaplan-Meier analysis will be done to estimate DFS and OS. The Cox proportional hazard model will be applied to estimate the hazard ratios and 95% confidence intervals. Although subjects were recruited according to the 2009 FIGO stage, the patients will be reclassified by the 2018 FIGO stage using the preoperative tumour size, and subgroup analysis will be performed.

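### The 13 events and 80% power count follow-up to 7.5 years; on the 4.5-year DFS endpoint, 111 to 124 evaluable patients give about 69% to 76% power

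*Protocol article*

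**What the plan says.** The Primary endpoint section defines the 4.5-year DFS rate as the "probability of no evidence of disease recurrence from the date of operation to the postoperative date of 4.5 years". The time window is closed, so a recurrence in year 5 or later does not enter it.

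The Sample size section states both hypotheses on that scale. Under H0 the rate in patients who "would undergo MIS using an endoscopic stapler is 83.7"%, and "the alternative hypothesis (H1) is that the 4.5-year DFS rate of the patients is 90.9"%. With three years of accrual and 4.5 years of follow-up, it concludes that "at least a total of 13 events must happen, requiring a total of 111 patients assuming a statistical power of 80"% with a one-sided 5% test. A 10% drop-out allowance raises the total to 124. The abstract repeats the event figure: "at least 13 events must happen, requiring a total of 111 patients".

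Under Statistical methods, "Kaplan-Meier analysis will be done to estimate DFS and OS". The article does not name the test behind the sample size.

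**The concern.** The endpoint, the two rates, the event count, the sample size and the power are all fixed in the same document, and they do not agree. With 90.9% disease-free at 4.5 years, 9.1% of 111 patients recur in the window, which is about 10 and not 13. If the extra events come from follow-up beyond the endpoint, the 80% power belongs to a different analysis from the one that the endpoint calls for.

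This is the only sizing given for the trial's main claim. At 69% power, the chance of missing a technique that truly matches open surgery is about 31%, where readers are told 20%. Wording 13 as a minimum that has to occur also invites misreading, because it is an expected count under H1 for one particular follow-up scheme.

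**Working it through.** **Inputs (Sample size section).** S0 = 0.837, S1 = 0.909, t = 4.5 years, one-sided alpha 0.05 (z = 1.645), power 0.80 (z = 0.842), accrual 3 years, follow-up 4.5 years, N = 111, drop-out 10%.

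**Assumptions for step 1 only.** Exponential DFS, uniform accrual, and follow-up until the last patient reaches 4.5 years, so that the first reaches 7.5.

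**1. Reproducing the stated figures.**

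- Hazards: λ0 = −ln(0.837)/4.5 = 0.03954 per year; λ1 = −ln(0.909)/4.5 = 0.02120 per year; ratio 0.536.
- Event probability over follow-up of 4.5 to 7.5 years: p = 1 − [exp(−4.5λ) − exp(−7.5λ)]/(3λ). This gives p0 = 0.2107 and p1 = 0.1193.
- Expected events under H1: 111 × 0.1193 = 13.2.
- One-sample exponential hazard test: n = (1.645·λ0/√p0 + 0.842·λ1/√p1)² / (λ0 − λ1)² = (0.1417 + 0.0517)² / (0.01834)² = 111.2, with 13.3 events. Power at 111 is 79.9%.
- One-sample log-rank test: events = HR(1.645 + √HR × 0.842)² / (1 − HR)² = 12.75, rounded up to 13. The n is 107 to 113, depending on the variance used. Power at 111 is 81.6% (simulated 81.4%).
- Drop-out: 111/0.9 = 123.3, rounded up to 124.

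The stated figures are therefore reproduced, but with follow-up beyond 4.5 years. None of the single-proportion formulas tried at 4.5 years gives 111: null and alternative variances 140, exact binomial 138, arcsine 130, complementary log-log 122 or 176, logit 169, alternative variance only 99, log scale 91.

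**2. The endpoint as defined.** With every patient followed to 4.5 years, this step needs neither the exponential nor the accrual assumption.

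- Expected recurrences in 111 patients: 111 × 0.091 = 10.1 under H1; 111 × 0.163 = 18.1 under H0.
- About 13.2 − 10.1 = 3.1 of the 13 events thus fall after the endpoint window. A Kaplan-Meier estimate at 4.5 years does not use them.

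| Rule at 4.5 years | Evaluable | Success if recurrences are at most | True one-sided alpha | Power |
|---|---|---|---|---|
| Exact binomial | 111 | 11 | 3.9% | 69.0% |
| Log-log limit | 111 | 11 | 3.9% | 69.0% |
| Plain-scale limit | 111 | 12 | 7.0% | 79.1% |
| Exact binomial | 124 | 13 | 4.6% | 76.3% |

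- Normal approximation at 111: Φ[(0.072√111 − 1.645√(0.837 × 0.163)) / √(0.909 × 0.091)] = Φ(0.525) = 70.0%.
- One-sample log-rank cut at 4.5 years, at 111: 69.2% (simulated 68.9%). Exponential hazard test cut at 4.5 years: 67.6%.
- Evaluable patients for 80% power: 138 (exact), 140 (normal), 141 (log-rank), 145 (hazard test).

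**3. Thirteen as a count.** If the true rate is 90.9%, the chance of 13 or more recurrences among 111 by 4.5 years is 21%. Over the full follow-up of step 1 it is 57%. Thirteen is an expected value under H1, not a minimum that the design guarantees.

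**The case against.** The strongest reply is that this is a condensed article and its analysis plan is not shown. The Statistical methods section uses Kaplan-Meier to estimate DFS and does not call it the primary test. Accrual plus follow-up is a usual input to a one-sample time-to-event design. If the full plan names such a test over all follow-up, 80% is about right for that test. This stands in part: the absence of a named test is not a fault here. But the endpoint and both hypotheses are still written as 4.5-year rates, and the power statement does not belong to them.

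Four stronger readings are tempting, and the document does not support them.

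- *That the design is a one-sample log-rank test.* This is an inference. The exponential hazard test fits 111 more closely. The conclusion is the same for both.
- *That power is simply 69%.* That is the figure for 111 evaluable patients. With all 124 evaluable it is 76%. Asymptotic tests at 111 range from about 63% to 77%, depending on scale and variance.
- *That reaching 13 events means failure, or that the analysis must wait for them.* With 13 of 111 recurring, the one-sided 95% lower limit is 82.0% (exact), 82.1% (log-log) or 83.3% (plain), all below 83.7%. With 13 of 124, however, the exact test succeeds. No rule ties the analysis or success to 13 events, so the phrase is best read as a loosely worded planning count.
- *That the type I error is inflated.* A full-follow-up test with a constant H0 hazard would give credit for late recurrence-free time. Simulations with the late hazard assumed at 50%, 25% or 0% of average gave error rates of roughly 11–12%, 18–20% and 26–29%. Neither the test nor those hazards is in the document, so the figures are illustrative only.

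**Conclusion.** The point holds in this form: the event count and power do not match the primary endpoint. On the 4.5-year DFS rate the design expects about 10 recurrences in 111 patients under H1 and 18 under H0. Its power, with a test that holds one-sided 5%, is about 69% with 111 evaluable and about 76% with 124, both below the stated 80%. The plain-scale limit's 79% is bought with a true alpha of 7%.

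The expected counts and the exact power rest only on the protocol's two rates and complete follow-up to 4.5 years. The explanation of where 13 and 111 come from rests on exponential DFS, uniform accrual and an inferred test, and should be presented as such.

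**What to change.** **Preferred.** Keep the 4.5-year DFS rate as primary endpoint and revise the Sample size section, the Statistical methods section and the abstract as follows:

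- The trial succeeds if the one-sided 95% lower limit for 4.5-year DFS, exact or log-log Kaplan-Meier, exceeds 83.7%. Without censoring this means 11 or fewer recurrences in 111, or 13 or fewer in 124.
- Power is about 69% with 111 evaluable patients and about 76% with 124.
- Replace the 13-event minimum with expected counts: about 10 recurrences by 4.5 years among 111 under H1, and about 13 only over full follow-up if DFS is exponential.

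This costs wording and a less favourable power figure, and no patients. If the sponsor wants 80% power on this endpoint, about 138 to 145 evaluable patients are needed, before any drop-out allowance.

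**Alternative.** Declare a one-sample time-to-event test over all follow-up as the primary test, and align the Primary endpoint section and the hypotheses with it. The H0 cumulative hazard curve should be specified over the whole follow-up and scaled to 83.7% at 4.5 years. The earlier open-surgery cohort's curve could supply the shape, but it passes through 90.9% and cannot serve as H0 unscaled. That curve is not in the article and would have to be obtained. The 13 should still be described as expected.

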### Patient discontinuation from the study

Patient withdrawal of consent. If it is judged that it is difficult to participate in this clinical trial due to the health of the patient. In case major clinical trial protocol violation or non-compliance is confirmed according to the evaluation of the principal investigator.There is no patient discontinuation based on the biopsy results after surgery (i.e. positive resection margin, positive metastatic lymph node, positive cytology etc.)

### Statistical methods

The efficacy analysis will be performed in both per-protocol and intention-to-treat populations. Kaplan-Meier analysis will be done to estimate DFS and OS. The Cox proportional hazard model will be applied to estimate the hazard ratios and 95% confidence intervals. Although subjects were recruited according to the 2009 FIGO stage, the patients will be reclassified by the 2018 FIGO stage using the preoperative tumour size, and subgroup analysis will be performed.

## Discussion

The SOLUTION trial focused on using an endoscopic stapler to prevent tumor spillage, considered the leading risk factor for poor prognosis in patients with early-stage cervical cancer treated with minimally invasive radical hysterectomy [3, 4]. Recently updated guidelines recommend that minimally invasive radical hysterectomy should not be preferred and that surgeons should conduct sufficient counseling with the patient before radical hysterectomy [5, 6]. A large-scale retrospective study reported that extracorporeal colpotomy during MIS showed the comparable efficacy to abdominal radical hysterectomy in the LACC trial (3-year DFS rate, 96.8% vs 97.1%; 3-year OS rate, 98.5% vs 99%) [13], suggesting the preventive effect of extracorporeal colpotomy on tumour spillage.

Tumour size can increase the risk of tumour spillage during intracorporeal colpotomy. Recent studies demonstrated that patients with less than 2 cm tumours showed no difference in survival between abdominal radical hysterectomy and MIS [16, 17]. In terms of eligibility criteria, we only included IB1 disease and excluded IA and IB2 disease. In the LACC trial, there was no evidence for a difference in survival according to the surgical approach in IB2 patients because patients with a tumour size of 4 cm or more were excluded from the study. Therefore, in our study, IB2 patients with tumour sizes greater than 4 cm were excluded. For patients less than 2 cm in diameter, as shown in several studies, there was no difference in survival between the two surgical methods, so patients with IA disease were excluded in the SOLUTION trial. Moreover, cervical conisation before radical hysterectomy showed a protective effect on disease recurrence [17, 18]. These findings suggest that the risk of tumour spillage during MIS increases as tumour size increases, which requires specific methods to prevent tumour spillage, such as the use of an endoscopic stapler in this trial. Even though the no-look, no-touch technique which encased the tumour within the upper vaginal cuff prevented tumour spillage with a similar survival benefit to adnominal radical hysterectomy [12], this technique can be conducted by only surgeons proficient in vaginal surgery and may not be feasible for women with the narrow vaginal orifice.

On the other hand, the effect of using a uterine manipulator on disease recurrence and survival is still controversial. The Surgery in Cervical Cancer, Observational, Retrospective (SUCCOR) study reported that no use of a uterine manipulator and the use of manoeuvres to avoid tumour spread at the time of colpotomy during MIS was related with comparable outcomes to open surgery [7]. In contrast, the other study showed that using a uterine manipulator was not a factor associated with disease recurrence and survival [19]. In the latter study, earlier stage patients including IA1-IB1 were enrolled, whereas the former included only IB1 patients. Therefore, the use of intrauterine manipulators in IB1 patients is considered to be associated with a higher risk of relapse, but there appears to be insufficient evidence of risk. So, we recommended that participating researchers will use a vaginal tube that does not penetrate through the cervical tumour. Even if they prefer a uterine elevator that requires a tip inserted through the cervical tumour, bilateral tubal ligation is required before the main surgical procedure to minimise the risk of tumour dissemination by using a uterine manipulator in this trial.

Furthermore, the inexperience of surgeons in using an endoscopic stapler during MIS can act as a bias in this trial. In the LACC trial, surgeons should have provided evidence of a minimal number of ten documented laparoscopic radical hysterectomies conducted and the outcomes of these operations with a video recording of at least one laparoscopic radical hysterectomy before they participated [3]. An ongoing Chinese phase III trial comparing the efficacy between abdominal radical hysterectomy and MIS requires at least 100 unselected, consecutive radical hysterectomy cases of investigators to qualify their skills and learning curves [20]. In the SOLUTION trial, TMC will verify the surgical experience of the participating investigators and the proficiency of using an endoscopic stapler to a similar extent to the two relevant trials. Furthermore, vaginal opening and vaginal closure after colpotomy are performed in the same way as laparoscopic hysterectomy; the risk of complications related to the surgical procedure is not expected to increase.

In terms of lymphadenectomy during SOLUTION trial, the investigators agreed to recommend systematic pelvic lymphadenectomy but permitted sentinel lymph node mapping during the surgery. First, SENTICOL II trial showed that sentinel lymph node mapping alone was not associated with worse outcomes than sentinel lymph node mapping with pelvic lymph node dissection [21]. Second, LACC trial protocol also allowed the operators to perform sentinel lymph node mapping and assessed the feasibility of sentinel lymph node biopsy [3]. These two studies support allowing sentinel lymph node mapping alone during the trial progression.

Currently, robot-assisted approach to cervical cancer (RACC) trial is recruiting early-stage cervical cancer (NCT03719547) [22]. This randomised non-inferiority trial protocol prohibits using uterine manipulators and recommends closing the vagina before colpotomy, but not mandatory. Although the RACC trial makes an effort to minimise tumour spillage in common with the SOLUTION trial, it compares the oncologic outcome of robot-assisted surgery to open surgery. On the other hand, SOLUTION trial is a phase II trial to evaluate the oncologic outcome of endoscopic vaginal stapling, either conventional laparoscopic or robotic. A randomised controlled trial comparing laparoscopic surgery with endoscopic stapling and laparotomy is needed based on the results of this study in the future.

The limitations of this study are as follows: first, the unexpected metastatic lesion may affect the washing cytology result. This should be interpreted with caution in conjunction with pathologic outcomes. Second, sentinel lymph node mapping and para-aortic lymphadenectomy were permitted and performed at the surgeon” discretion. Up to now, limited Evidence supports performing surgical staging for early-stage cervical cancer; still, there are chances to detect small volume metastasis, the prognostic role is not well elucidated. Therefore, each investigator will decide whether to perform para-aortic lymphadenectomy or not according to the patient status, such as large tumour volume, elevated tumour markers, etc. Third, 4.5-year DFS instead of 5-year DFS is used for the primary endpoint, not conventionally used as a trial endpoint. However, using a 4.5-year DFS, we can attain a primary endpoint with minimal sample size, follow-up period, and comparable results with LACC trial.

To summarise, we expect that intracorporeal colpotomy using an endoscopic stapler may prevent tumour spillage during minimally invasive radical hysterectomy for stage IB1 disease. Moreover, we will perform the peritoneal washing cytology three times during MIS as follows: before insertion of a uterine manipulator; before intracorporeal colpotomy after resecting the vagina using the endoscopic stapler; after the closure of the vaginal stump. Preoperative cytology will be able to evaluate the presence of microscopic tumors in the abdominal cavity before surgery. We also expect to detect tumour spillage through consecutive peritoneal washing cytology and will evaluate how the detection of tumour spillage would affect the prognosis and recurrence pattern in this trial.

